## Abstract

**Background:**

Delays in reviewing issued laboratory results in emergency departments (EDs) can adversely affect efficiency and quality of care. One opportunity to improve therapeutic turnaround time could be to provide real-time access to laboratory results on mobile devices available to every caregiver. We developed a mobile app named “Patients In My Pocket in my Hospital” (PIMPmyHospital) to help ED caregivers automatically obtain and share relevant information about the patients they care for including laboratory results.

**Objective:**

This pre- and posttest study aims to explore whether the implementation of the PIMPmyHospital app impacts the timeliness with which ED physicians and nurses remotely access laboratory results while actively working in their real-world environment, including ED length of stay, technology acceptance and usability among users, and how specific in-app alerts impact on its effectiveness.

**Methods:**

This single-center study of nonequivalent pre- and posttest comparison group design will be conducted before and after the implementation of the app in a tertiary pediatric ED in Switzerland. The retrospective period will cover the previous 12 months, and the prospective period will cover the following 6 months. Participants will be postgraduate residents pursuing a ≤6-year residency in pediatrics, pediatric emergency medicine fellows, and registered nurses from the pediatric ED. The primary outcome will be the mean elapsed time in minutes from delivery of laboratory results to caregivers’ consideration by accessing them either through the hospital’s electronic medical records or through the app before and after the implementation of the app, respectively. As secondary outcomes, participants will be queried about the acceptance and usability of the app using the Unified Theory of Acceptance and Use of Technology model and the System Usability Scale. ED length of stay will be compared before and after the implementation of the app for patients with laboratory results. The impact of specific alerts on the app, such as a flashing icon or sound for reported pathological values, will be reported.

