### Participants

Eligible participants will be postgraduate residents pursuing a less than 6-year residency in pediatrics, pediatric emergency medicine fellows, and registered nurses from the pediatric ED (aged >18 years). Written informed consent will be obtained from each participant in the experimental group after full information disclosure prior to study participation. On the first day, after completing the informed consent form, participants will be asked to download the app to their personal smartphone through the secure institutional Microsoft Intune portal (Microsoft Corporation). They will then be required to attend a unique standardized 5-minute introduction course to the app and its functionality by the study investigators, but they will not receive specific instructions on how often to use the app. The participants will remain the same throughout the intervention period. No one will be asked to advise on the interpretation of the results.

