### Procedure and Intervention

This is a pre-post study. Before the implementation of the app, EMR-based data from the past 12 months will be collected retrospectively. These data will include the times (ie, HH:MM:SS) that results issued by the central laboratory were available on the institutional EMR as well as the times at which these results were accessed by caregivers through conventional computerized workstations. After the implementation of the app, data will be collected prospectively over a 6-month period of use. This will include the times (HH:MM:SS) when the results issued by the central laboratory are made available through the app on caregivers’ smartphones and access times as well as concurrent or preferred access times on the conventional computerized workstations should this occur. Individual acceptance of the app on the first day (a priori) and then on the last day of the intervention will be evaluated through the Unified Theory of Acceptance and Use of Technology (UTAUT) [23]. Usability of the app will be measured by the System Usability Scale (SUS) [24]. Figure 1 shows the study procedure, and Table 2 presents the study schedule. Use of the app will be on a 24-hour basis and at the discretion of participants.

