**Assessments**					
	Case report form (demographics)		✓		
	EMR^b^-based data	✓	✓	✓	
	App-based data		✓	✓	
	UTAUT^c^		✓		✓
	SUS^d^				✓

^a^✓: Performed.

^b^EMR: electronic medical record.

^c^UTAUT: Unified Theory of Acceptance and Use of Technology.

^d^SUS: System Usability Scale.

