### Outcomes and Measures

#### Primary Outcome: Time to Laboratory Access

The primary outcome will be the mean elapsed time in minutes between the delivery of the laboratory results and the caregiver accessing them, both before and after the implementation of the app.

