### Statistical Analysis

The association of app use with the time between delivery of the laboratory results and their access by caregivers will be assessed using generalized estimating equations with an exchangeable correlation structure to account for the nested structure of the outcome (ie, time) within the physicians. To account for potential differences in case-mix and physician characteristics, we will use multivariable generalized estimating equations. The covariates will be as follows: (1) the triage acuity scale, (2) type of pathology (medical, surgical-traumatological, psychiatric), (3) experience of the caregiver expressed in years since certification, (4) patient age, (5) patient sex, (6) workload represented by the number of patients present in the emergency room, (7) time of day or night, (8) day of the week, and (9) month of the year (seasonal variability). To account for the possible effect of exogenous factors that would impose an asymmetry in the data (skewness on the right) by extending the awareness of laboratory results, we will identify these factors as the study progresses prospectively and take them into account in the final analysis. The same analyses will be performed for the nurses. We will carefully monitor and evaluate through descriptive analyses any differences between nurses’ and physicians’ frequency access to laboratory results. If the target sample size cannot be reached, we will first extend the prospective data collection period by 3 months (deemed ethically acceptable as not impacting patients) or present only the results of qualitative user experience interviews.

For the technology acceptance self-administered survey questionnaire, scores on the 8 technology acceptance constructs will be described using descriptive statistics. Items on the SUS questionnaire will be described using frequencies. Analyses will be carried out using R software (R Core Team) [27]. All statistical tests will be 2-sided, with an α risk of .05.

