### Limitations

This study has some limitations. First, participants who agree to be prospectively enrolled may be interested or engaged in digital health promotion in general and mobile technologies in particular, influencing their a priori motivation to use the app. If so, this should be reflected in the UTAUT questionnaire, which is an outcome of interest. Second, the study will be conducted in a pediatric ED, which may limit the generalizability of the findings to adult EDs. For example, the acuity of age-specific diseases may imply a different awareness in the consideration of laboratory results. Other limitations may be identified during the study itself and will be noted after their identification.

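### The primary outcome and exposure are defined inconsistently: some sections set EMR access before against app access after, others describe a before/after contrast by any route, and no rule says which time stamp counts

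*Protocol article*

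**What the plan says.** **Text pointing to EMR before versus app after, or to app use.** The abstract (Methods) describes access through the hospital's "electronic medical records or through the app before and after the implementation of the app, respectively". The Objectives section gives the comparison as remote access through the app against standard access before implementation. The Statistical Analysis section will estimate "The association of app use with the time between delivery of the laboratory results and their access by caregivers". The Discussion (Strengths and Perspectives) expects shorter times in participants who use the app than in people who had not used it before.

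**Text pointing to a period contrast by any route.** The abstract's Objective asks about the impact of implementing the app. Study Design compares a 12-month period before with a 6-month period after. The Primary Outcome section names no route: "mean elapsed time in minutes between the delivery of the laboratory results and the caregiver accessing them, both before and after the implementation of the" [PIMPmyHospital app]. Procedure and Intervention says that post-period data will include app "access times as well as concurrent or preferred access times on the conventional computerized workstations should this occur". Table 2 ticks EMR data at pretest, at implementation and at posttest.

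**Time stamps.** Data Collection introduces first access to the EMR results viewer in the context of the preintervention period. It gives a separate rule for the app (opening the push notification or the results page). It does not say how the two combine.

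**Who is included.** "Written informed consent will be obtained from each participant in the experimental group", and "Use of the app will be on a 24-hour basis and at the discretion of participants". The EMR access rule refers to the physicians and nurses, with no stated restriction to those who later enrol. Limitations concedes that enrolled participants may be keener on mobile technology and adds: "If so, this should be reflected in the UTAUT questionnaire, which is an outcome of interest".

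**The concern.** The study question is whether implementing the app changes the time caregivers take to see results. Whether a given result is opened in the app is decided by the caregiver after implementation. An analysis that counts app openings only, or that takes app use as the exposure, therefore selects post-period results on a behaviour that follows the intervention, and it compares them with a pre-period that has no such selection. That is a different question from the stated one, and its answer can differ greatly from the effect of implementation.

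The caregivers may differ too. Post-period participants are consenting enrollees, while no matching restriction is stated for the pre-period. The questionnaire that Limitations relies on to reveal this is completed only by those who enrol.

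As the text stands, either contrast could be presented as the planned primary analysis, and the choice could be made after the data are seen.

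**Working it through.** **1. The sections side by side**

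| Section | Outcome or exposure implied |
|---|---|
| Abstract, Methods | EMR before, app after |
| Objectives | App access versus earlier standard access |
| Statistical Analysis | App use (not defined as period or as actual use) |
| Discussion, Strengths and Perspectives | Users versus earlier non-users |
| Abstract, Objective | Implementation |
| Study Design | Period before versus period after |
| Primary Outcome | Access by the caregiver, no route named |
| Procedure and Intervention; Table 2 | App and workstation access both recorded after implementation |
| Data Collection | Separate EMR and app rules, none to combine them |

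The first four rows and the next four cannot all describe the same primary contrast.

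**2. The plan's own figure.** Sample Size gives 0.5 SD, 90% power, 5% level and an intraclass correlation of 0.1, with 100 patients a month for 3 months, so 300 per physician. Two equal groups, two-sided: 85 per group, 170 in total. Design effect: 1 + (300 − 1) × 0.1 = 30.9. Then 170 × 30.9 = 5253, as stated, and 5253 / 300 = 17.5, so 18 physicians. The figure reproduces. It assumes a difference of 0.5 SD without saying by which route.

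**3. How far the two contrasts can part.** Input from the article: the 92% reduction in the semisimulated pilot (Previous Work). Assumptions: app-opened results are seen 92% faster, the others are unchanged, and uptake is 20% to 80%, since the article gives no uptake. Period effect = uptake × 0.92.

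| Uptake | Period effect | App-only analysis |
|---|---|---|
| 20% | 18% | 92% |
| 40% | 37% | 92% |
| 60% | 55% | 92% |
| 80% | 74% | 92% |

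**4. Direction of the error when the app does nothing.** Assumptions: log-normal access times (log-mean 2.5, log-SD 1, mean about 20 minutes) and no app effect. Propensity to open in the app has correlation r with log time, and only app-opened results are analysed. Simulated shift in the post-period mean, in SD units:

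| Uptake | r = −0.3 (quicker results favoured) | r = 0 | r = +0.3 (slower results favoured) |
|---|---|---|---|
| 30% | −0.24 | 0.00 | +0.28 |
| 50% | −0.18 | 0.00 | +0.18 |
| 70% | −0.12 | 0.00 | +0.10 |
| 90% | −0.05 | 0.00 | +0.04 |

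A second mechanism hides a real gain. Suppose each result can be reached by both routes, with independent exponential times of mean 20 minutes each. First access by either route averages 1 / (1/20 + 1/20) = 10 minutes. The app time stamp alone averages 20 minutes, the same as EMR-only access before, so an app-only clock would show no change where the true mean was halved.

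**5. What dilution costs in power.** Assumption: a 0.5 SD gain on app-opened results and none on the rest. Difference = uptake × 0.5 SD, put through the plan's own formula (equal groups, design effect 30.9):

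| Uptake | Difference | Patients |
|---|---|---|
| 30% | 0.15 SD | 57,721 |
| 50% | 0.25 SD | 20,827 |
| 70% | 0.35 SD | 10,630 |
| 90% | 0.45 SD | 6,427 |

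**6. The questionnaire.** Procedure and Intervention and Table 2 place the UTAUT at implementation and at the end of the study, for participants. Those who decline and pre-period staff have no scores, so there is nothing to compare enrollees with.

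**The case against.** A reader might infer that results not opened in the app are dropped and that the effect is therefore inflated. The article supports neither step. Post-period workstation access is explicitly collected and nothing says it will be excluded. Inflation would need both an app-only analysis and quicker results being favoured in the app; under other assumptions the error is nil or reversed. It is likewise only an inference from silence that the pre-period covers every caregiver in the EMR log.

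It can also be said that the body definition of the primary outcome is neutral on route, that app use may simply mean the period after implementation (Study Design can be read that way), and that a rule for combining time stamps may sit in an unseen analysis plan. The design is labelled nonequivalent, volunteer selection is the first limitation named, and the model adjusts for case-mix and caregiver experience.

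Much of this stands. It rules out any claim about direction or size, and the missing combination rule alone would be a matter of detail. It does not remove the conflict. Four places, including the stated comparison in Objectives and the model's exposure, lean towards route or use, and an unseen plan does not reconcile wording that disagrees within this document. Disclosing volunteer selection does not repair the remedy offered for it, and none of the listed covariates measures willingness to enrol.

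**Conclusion.** The primary outcome and exposure are fixed inconsistently, and the time stamp that counts is left open when a result is opened by EMR, app or both. If the wording of the abstract's Methods and of Objectives is followed, the primary contrast is conditioned on discretionary app use by consenting participants and does not answer the implementation question. If the period wording is followed with first access by any route, that problem does not arise.

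The article gives neither uptake nor a distribution of access times, so no size can be derived from it. The 18% to 74% against 92% rests on assumed uptake and on carrying a semisimulated pilot result into practice. The shifts of up to about 0.3 SD either way rest on an assumed shape and correlation. They show only that the two readings can differ materially. Separately, the UTAUT cannot show how enrolled participants differ from those who declined or from pre-period staff.

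**What to change.** - Reconcile the abstract's Methods, Objectives, Statistical Analysis and Discussion with the abstract's Objective, Study Design, Procedure and Intervention, Table 2 and Primary Outcome.
- Define the outcome in both periods as time from delivery of the result to first access by any available route: EMR before, and the earlier of EMR and app after.
- Make period (before or after implementation) the primary exposure, in caregiver groups defined the same way in both periods, for example by role rather than by enrolment.
- Report actual app use as a secondary analysis.
- In Limitations, drop the suggestion that the UTAUT will reveal volunteer selection.

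The cost is mainly wording and some analysis work, since EMR data are already planned for both periods. If groups are defined by role, it must be checked that post-period EMR logs of staff who do not enrol may be used. The main downside is dilution: the effect may be smaller than the 0.5 SD behind the 5253 patients, so the sample size should be revisited with a stated uptake assumption. Treating never-opened results as censored at ED departure is not part of this change, because it would not fit the planned generalized estimating equations on elapsed time.

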**Results:**

Retrospective data collection gathered from the institutional data set will span a 12-month period from October 2021 to October 2022, while the 6-month prospective collection will begin with the implementation of the app in November 2022 and is expected to cease at the end of April 2023. We expect the results of the study to be published in a peer-reviewed journal in late 2023.

**Conclusions:**

This study will show the potential reach, effectiveness, acceptance, and use of the PIMPmyHospital app among ED caregivers. The findings of this study will serve as the basis for future research on the app and any further development to improve its effectiveness.
Trial Registration: ClinicalTrials.gov NCT05557331; https://clinicaltrials.gov/ct2/show/NCT05557331

**Trial Registration:**

ClinicalTrials.gov NCT05557331; https://clinicaltrials.gov/ct2/show/NCT05557331

**International Registered Report Identifier (IRRID):**

PRR1-10.2196/43695

## Introduction

### Background

Emergency department (ED) overcrowding is a global health problem [1], leading to prolonged ED length of stay (ED-LOS). ED-LOS is the time interval between the patient’s arrival in the ED for registration or triage to disposition from the ED, either to be admitted to a hospital, discharged home, or transferred to another care setting. ED-LOS is considered as a key indicator of the performance, quality, and operational efficiency of an ED and, more broadly, the entire hospital to which the ED belongs [2]. It also serves as a benchmark metric between institutions. Prolonged ED-LOS, that is, stays exceeding 6 hours (with cutoffs ranging from 4 to 48 hours [3]), can adversely affect efficiency and quality of care, patient outcomes, and patient satisfaction [4].

According to the conceptual input-throughput-output model proposed by Asplin et al [5], ED congestion is partitioned into 3 interdependent components in terms of patient flows into, through, and out of the ED, respectively. The entire laboratory testing process, also known as therapeutic turnaround time (TAT) and part of the throughput component, is a major contributor to prolonging ED-LOS [6,7]. Laboratory tests are ordered in nearly 48% of ED visits [8], and 70% of patient-management decisions are based on these tests [9]. Numerous mitigation strategies to minimize the intralaboratory analytic time, such as laboratory automation and digitalization, have been implemented [10,11]. Yet, it is estimated that up to 96% of the delays that contribute to the therapeutic TAT occur in the pre- and postanalytical phases outside of the central laboratory [12,13]. In the latter case, caregivers’ delayed awareness and timely review of available laboratory results have been described as the largest component of perceived therapeutic TAT [11], strongly contributing to prolonged hospital LOS [14]. This delay may be partly related to the fact that busy, multitasking ED physicians and nurses are cognitively distracted from reviewing laboratory results in a timely manner in the absence of individualized, automated real-time prompts. Prompt awareness of results’ availability in real time requires health care personnel to regularly access electronic medical records (EMR), leading to incessant and time-consuming trips to computer workstations, thus distracting them from patient care in an extremely challenging and changing environment.

### Previous Work

Targeted interventions to reduce the postanalytical TAT phase may contribute to shortening ED-LOS, but mobile digital health solutions to achieve this goal are scarce. In a previous study [15], we described the user-centered development and early technology acceptance evaluation of a mobile app called “Patients In My Pocket in my Hospital” (*PIMPmyHospital*). The app was designed to help ED caregivers obtain relevant information in real time for the patients they care for, including laboratory and imaging results. The app also offers an end-to-end encrypted chat to provide a remote communication channel between caregivers caring for the same patients. In a randomized controlled pilot trial [16], the time required for ED physicians and nurses to review laboratory results after their release was significantly reduced by 92% using the app compared to the usual procedure in a semisimulated model. However, the potential effectiveness of this app in mitigating ED-LOS by taking cognizance of laboratory results in a shorter time frame than usual remains to be evaluated in daily clinical ED practice.

### Objectives

In this study, we present the protocol for a pre- and posttest study. Its objective is to evaluate whether the use of the *PIMPmyHospital* app alters ED physicians’ and nurses’ temporal efficiency to access laboratory results more quickly while actively working in an ED. Temporal efficiency will be assessed by measuring the time between the release of the laboratory results in the clinical information system and their acknowledgment by these clinicians. To our knowledge, no app that can access laboratory results in real time in the ED has been described to date [17]. The study will be structured according to the “Population,” “Intervention,” “Comparison,” and “Outcome” framework as follows: (1) participants: medical and nursing staff working in the pediatric ED; (2) intervention: implementation of the mobile app in the pediatric ED; (3) comparison: remote access to laboratory results in the pediatric ED through the app versus standard access to laboratory results prior to its implementation; (4) outcomes: times to access laboratory results, ED-LOS, technology acceptance, and app’s usability among users, and how specific in-app alerts impact on its effectiveness.

## Methods

### Study Design

We will conduct an 18-month, single-center, nonequivalent comparison group, pre-post study. We will compare the control and experimental groups on outcome measures before (12-month period) and after (6-month period) the implementation and use of the app. This study protocol adheres to the Standard Protocol Items: Recommendations for Interventional Trials 2013 Checklist [18]. All data will be deidentified. The study will be conducted according to the principles of the Declaration of Helsinki [19] and Good Clinical Practice guidelines [20]. It is our intention to present these at scientific congresses and to publish the results in an international peer-reviewed journal, irrespective of the magnitude or direction of effect. Only deidentified data will be available to researchers for analysis. The study is registered at ClinicalTrials.gov on September 28, 2022 (NCT05557331).

